## Abstract

**Background:**

Coping with a chronic illness (CI) challenges children's psychosocial functioning and wellbeing. Cognitive-behavioral intervention programs that focus on teaching the active use of coping strategies may prevent children with CI from developing psychosocial problems. Involvement of parents in the intervention program may enhance the use of learned coping strategies in daily life, especially on the long-term. The primary aim of the present study is to examine the effectiveness of a cognitive behavioral based group intervention (called 'Op Koers') [1] for children with CI and of a parallel intervention for their parents. A secondary objective is to investigate why and for whom this intervention works, in order to understand the underlying mechanisms of the intervention effect.

**Methods/design:**

This study is a multicentre randomized controlled trial. Participants are children (8 to 18 years of age) with a chronic illness, and their parents, recruited from seven participating hospitals in the Netherlands. Participants are randomly allocated to two intervention groups (the child intervention group and the child intervention combined with a parent program) and a wait-list control group. Primary outcomes are child psychosocial functioning, wellbeing and child disease related coping skills. Secondary outcomes are child quality of life, child general coping skills, child self-perception, parental stress, quality of parent-child interaction, and parental perceived vulnerability. Outcomes are evaluated at baseline, after 6 weeks of treatment, and at a 6 and 12-month follow-up period. The analyses will be performed on the basis of an intention-to-treat population.

**Discussion:**

This study evaluates the effectiveness of a group intervention improving psychosocial functioning in children with CI and their parents. If proven effective, the intervention will be implemented in clinical practice. Strengths and limitations of the study design are discussed.

**Trial registration:**

Current Controlled Trials ISRCTN60919570

## Background

Improvements in pediatrics and childhood surgery result in an increase of children surviving serious diseases. Consequently the number of children living with a chronic health condition is increasing drastically. Estimated prevalence ranges to a maximum of 44% (in the Netherlands approximately 500.000 (at least 14%)) [2]. Children with CI and their families face a lifetime of medical treatment and uncertainty about the future. They often have to cope with frequent hospitalizations, painful medical procedures, pharmacological interventions, school absenteeism, and restriction of activities due to the medical treatment [3]. As a result, these children may suffer from a multitude of short and long-term cognitive, behavioral and emotional problems (e.g. rumination, attention problems, and lower self-esteem) and social maladjustment. Children with CI show more submissive behavior and tend to be more socially withdrawn, in particular when they use avoidant or passive coping strategies [4].

Therefore, intervention programs that are effective in learning active coping skills to children with CI, may help to reduce psychosocial problems in these children. Based on an overview of the published research on the efficacy of available interventions there is evidence that, in general, psychological interventions produce promising positive results [5,6]. However, little is known about the mechanisms of change of these interventions and about the medium- and long-term effects. Authors also criticize the small sample sizes, the lack of correspondence between treatment objectives and their measurement, and the lack of external validation of findings [7]. Described interventions were mostly developed for a single diagnosis, such as diabetes or asthma. However, forming homogenous groups excludes underrepresented populations, and limits the sample size, which in turn limits the possibilities to prove the effectiveness and the generalizability of the program to other groups. Also children with CI may have different diagnoses and different medical treatments, but the psychosocial challenges (e.g., frequent hospitalizations, school absenteeism, restriction of activities) are mostly the same. Therefore, there should be focus on the similarities between children with chronic illness, rather than the differences between diagnosis groups [7].

Considering the limitations of existing interventions for children with CI, a standardized group-based intervention program has been developed for heterogeneous groups of children with CI, called 'Op Koers' (in English: On Track). This intervention program comprehends the learning of active coping skills, based on a cognitive behavioral approach, with the aim to support resilience and prevent psychosocial problems. A first pilot study, with 109 children and adolescents, showed positive changes on the children's wellbeing 6 months post intervention. Patients reported significantly more relaxation and positive thinking, higher social competence, and more information seeking than before the intervention [1]. Positive findings were also repeated in a homogenous group of children with inflammatory bowel disease (IBD), compared to a small control group [8]. However, in these studies outcomes were not compared to a control group and the effect sizes for disease related coping skills were relatively small. Furthermore, the intervention did not include parents, while the effects of child directed interventions can be improved by parallel programs for parents [9]. Parental support is associated with decreased levels of distress during medical procedures [11] and increased psychosocial adjustment [10] in children with CI. However, some parents of children with CI may tend to control their children and constantly try to protect them, possibly leading to adjustment problems caused by limited autonomy development [12]. Finally, parents may avoid talking with their children about negative emotions related to the disease, such as anxiety for the course of the disease, uncertainty about future (education or work) and sadness about victimization by peers. Therefore, educating parents about the importance of parental support, by learning them to talk with their child about emotions, listen and accept the child's feelings, and support and motivate the child's autonomy is expected to enhance the effect of the child intervention, especially on the medium- and long-term. As a result, a well-balanced intervention for parents was developed, parallel to the child intervention.

To assess whether the intervention program 'Op Koers' is effective, a randomized controlled trial is required. This paper describes the rationale and the design of this study. The objective is to assess the extent to which 'Op Koers' is effective in increasing or stabilizing psychosocial wellbeing in children (8-18 years) with a chronic illness, and to examine the extent to which a newly developed parental intervention enhances the effect. Primary outcomes are child psychosocial functioning, wellbeing and child disease related coping skills. Potential mediating and moderating variables are investigated in order to identify predictors of treatment effect and to evaluate potential underlying mechanisms of change [13]. Several moderating factors, such as medical characteristics (severity of the illness, diagnoses), psychological characteristics (involvement of the participant in the program), and specific characteristics (type of hospital, organization of the program, compliance to the manual) will be explored. Type of diagnoses was not related to treatment effects in the pilot study, and will be tested as a control variable in the present study. Potential mediating factors are; child quality of life, child general coping skills, child self-perception, parental stress, quality of parent-child interaction, and parental perceived vulnerability.

## Methods/design

### Interventions

#### Child intervention 'Op Koers'

'Op Koers' is based on techniques proven to be effective in behavioral and cognitive behavioral programs for children with somatic complaints [14] and in children with behavior and/or anxiety disorders [14]. 'Op Koers' has slightly different versions for two different age groups because of differences in cognitive development and age related topics. The first group consists of primary school children (8-12 years) and the second of adolescents in secondary school (12-18 years). The intervention takes place in the hospital were the child is medically treated, and involves six weekly 90 minutes sessions, and one return session after six months. To stimulate group processes and because of educational reasons groups with a minimum of four and a maximum of eight children are formed. The intervention aims to empower children with CI by teaching the active use of coping strategies. These coping strategies are translated into five learning goals: 1) information seeking and information giving about the disease ('good to know better' principle), 2) use of relaxation during stressful situations (using exercises), 3) increase knowledge of self-management and compliance, 4) enhancement of social competence (group discussions, role playing), and 5) positive thinking (effective use of the Thinking-Feeling-Doing model; replacement of inaccurate thoughts) [14]. During the group sessions the goals are translated into psycho-education (such as informative video's and group discussions), and reinforced and practiced through exercises (such as role-play and board games) and homework assignments. In all sessions age-appropriate examples are used.

#### Parent intervention

The parent intervention is built on existing cognitive behavioral programs for parents of children with anxiety problems [15,16] and on outcomes from several parent focus groups and expert clinical advisory groups. Primary purpose of the parental module is enhancing intervention effects of the children's program, by teaching parents to be sensitive to their children's needs, and encourage their children in using the learned skills. Overall, the parent intervention is intended to change the context for the child. This is done by enhancing availability of parental support as perceived by the children, expected to result in increases in children's perceived self-esteem and in the use of active coping skills in daily life as well as in situations related to their disease and treatment, which in turn will improve social-emotional functioning. The parent intervention fits into the learning goals of the child intervention. Three learning goals are central to the parent training: 1) Learning: to understand what the children learn (psycho education, group discussions), 2) Observing: to be sensitive to children's cognitions and feelings (by assignments to talk about feelings with their child), 3) Motivating: to stimulate their children to apply the learned skills in daily life (by assignments to support their child to ask questions to the doctor). To limit the number of visits to the hospitals and to enable shared homework assignments, the parent intervention groups are organized at the same time as the intervention groups of their child, in another room.

The content of the child and parent interventions is summarized in Table 1.

**Table 1 T1:** The five basic learning goals of 'Op Koers' (child and parent intervention) and examples of learning activities in the child and parent intervention programs.

	Examples Of learning Activities\Five Basic learning Goals	Information seeking and information giving about the illness	Use of relaxation during stressful situations	Increase knowledge of self-management and compliance	Enhancement of social competence	Positive thinking
Examples of learning activities of the child intervention	Instruction/modeling	Education about sources of information	Relaxation exercise (CD)/practicing tricks for medical procedures (video)	Discussion about own treatment and (non) Compliance	Video: take initiative and inform	Thinking-feeling-doing game
	
	Reinforcement/Practice	Role play: ask your own questions to your pediatrician	Homework: practice the relaxation exercise	Group exercise: make a drawing about your treatment	Role play: inform peers about what you cannot and what you CAN do instead	Homework: write down your negative thoughts and explore ways to get rid of them

Examples of learning activities of the parent intervention	Instruction/modeling	Education about sources of information	Relaxation exercise (CD)	Group discussion about what to do when your child has problems with compliance	Video: take initiative and inform	Introducing Thinking-feeling-doing model
	
	Reinforcement/Practice	Homework: stimulate and support your child to find and give their own answers about their illness	Homework: observe and ask your child about a stressful situation and talk about what to do	Homework: talk with your child about treatment and find out the reasons for non-compliance	Homework: practice with your child how to ask other children to play together	Talk about cognitions with your child and help to find positive thoughts

### Study design

The design is a multi centre randomized controlled trial with three conditions: 1) the child intervention group 'Op Koers', 2) the child intervention with a parallel parent program, and 3) a wait-list control group. Subjects in the control condition are placed on a one year waiting list. After the 12 months follow-up they have the opportunity to participate in the intervention. Participants assigned to the control group are not prevented to seek individual treatment, but the participating hospitals are advised to wait with individual psychological treatment until after the follow-up assessment. If the child or the family needs acute psychological care, this will be approved. It will be extensively documented and controlled in the analyses, when children and/or parents receive treatment during this period.

This study was approved by the Medical Ethics Committees of the Academic Medical Centre Amsterdam and of the participating hospitals.

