### Sample size

The expected effect size and attrition rates are based on former trials that studied the effects of cognitive-behavioral group interventions for children with CI. Generally, psychological interventions for children with CI indicated medium effect sizes (mean ES = 0.71, range = 0.28-3.23, SD = 0.61) [6]. In a study that evaluated cognitive-behavioral group interventions for children with anxiety disorders, enhanced by parental involvement also medium effect sizes were found [19]. Based on four repeated measurements with within-subject correlations of .5, a sample size of 126, 42 in each condition, is necessary to achieve adequate power (.80) to trace differences of medium effect size (d = .5) between the conditions over time at a significance level of .05 [20]. To be able to control for dependency effects (block and centre effects) and taking into account 10% attrition over time, 162 children have to be recruited to reach the required sample size.

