### Statistical analyses

The analyses will be performed on the basis of an intention-to-treat population. Treatment effects (group × time) will be assessed with linear mixed model analysis using SPSS. Intraclass correlations will be computed to test possible dependency effects of block randomization [35]. In secondary analyses, mediator variables will be included to investigate which underlying processes in children and families change as a result of the intervention. Moderator variables will be included to examine whether the effects are associated with characteristics of the child and the family (gender, age, medical diagnosis, severity of disease, attendance during group sessions).

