## Discussion

This paper outlines the study protocol for a multicentre randomized controlled trial on the effects of a cognitive-behavioral based group intervention for children with chronic illness and their parents. Former studies have shown that psychological interventions for children and adolescents with chronic medical conditions can improve social-emotional functioning [5,6]. However, more research is needed into the effectiveness of such programs with a large sample size, adequate methodological and statistical analyses and an extended follow-up. Although it is known parental involvement enhances the use of coping strategies by the child [19] studies on interventions for parents, specifically directed at parental support and behavior, are limited [36]. Therefore the strength of the 'Op Koers' intervention is that it focuses on both the coping strategies of the child and manipulates the level of parental support. This will allow testing the assumption that involving the context bolsters long-term effects.

Another strength of the present study is that by focusing on heterogeneous groups (children with different medical diagnoses), and by including multiple centers, it is possible to include a relatively large sample size, sufficient for comparing the two intervention conditions to the control group. Also the use of a stratified block randomization method achieves to overcome practical difficulties that are common in these kinds of trials. To understand why and for whom the intervention may work, the effects of mediating and moderating factors are investigated, which makes it possible to further develop and extend the intervention program. Other strong aspects of the study are the number of assessments, and the relatively long term follow-up.

This study design has several methodological vulnerabilities. First, because of the randomization into three cohorts and the two different age groups, it may take a significant time period to recruit enough participants. This can increase the time between recruitment and actual participation and may lead to dropout attrition. Second, due to the relatively long follow-up period it is possible that participants within the control group, as well as participants in the intervention groups during the follow up period, will seek other psychosocial support. These limitations have to be taken account in data analyses.

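### Psychological treatment received during follow-up is to be controlled in the analyses without restricting this to a supplementary analysis; read plainly, the comparison then no longer estimates the effect of assignment

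*Protocol article*

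**What the plan says.** Under Study design, controls wait one year. On other care in that time: "Participants assigned to the control group are not prevented to seek individual treatment, but the participating hospitals are advised to wait with individual psychological treatment" (the advice runs to the end of the waiting year), and "If the child or the family needs acute psychological care, this will be approved". The paragraph closes with the commitment at issue: "It will be extensively documented and controlled in the analyses, when children and/or parents receive treatment during this period".

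The Discussion widens this to all arms. It names as a limitation the possibility that "participants within the control group, as well as participants in the intervention groups during the follow up period, will seek other psychosocial support", and adds: "These limitations have to be taken account in data analyses".

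Under Statistical analyses: "The analyses will be performed on the basis of an intention-to-treat population" and "Treatment effects (group × time) will be assessed with linear mixed model analysis using SPSS". The secondary analyses listed there concern mediators and moderators. Other psychological care is not among them, and no section says in which analysis it is to be controlled, by what method, or to answer which question.

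**The concern.** Other psychological care starts after randomisation, and the article ties it to two things. One is allocation: the advice to wait appears in the sentence about controls. The other is need: acute care is approved when the child or family needs it. A variable that follows allocation and also marks a poor course is not a baseline covariate. With it in the model, the arm coefficient compares children who had the same care status, and those groups are no longer balanced by randomisation. The coefficient is then not the effect of assignment. It is not a clean effect in the absence of other care either, because need drives both the care and the outcome.

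At stake is the headline comparison. The article's conclusion ties implementation of the programme to significant improvement in this trial.

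**Working it through.** **Inputs from the article (Sample size section).** 42 children per condition, d = 0.5, power 0.80, significance level 0.05 (two-sided assumed), and "Based on four repeated measurements with within-subject correlations of .5". The article gives no uptake of other care, no effect of it and no referral rule. These are assumed below and varied.

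**The plan's own figure.** For the mean of the three post-baseline measurements with correlation 0.5, the variance factor is (1 + 2 × 0.5)/3 = 0.667. Then n = 2 × (1.960 + 0.842)² × 0.667 / 0.5² = 41.9, so 42 per arm and 126 in total. The standard error is √0.667 × √(2/42) = 0.178, and power is Φ(0.50/0.178 − 1.96) = 0.80. The plan's figure reproduces, and it does not depend on how other care is handled.

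**What adjustment does.** Take outcome on arm and baseline (ITT model), then add an indicator of other care with coefficient k. With uptake p_c in controls and p_a in the active arm, in large samples:

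adjusted − ITT = k × (p_c − p_a)

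The shift is zero if uptake is equal or if k = 0. Because care goes to children who are doing poorly, k mixes a negative part (need) with any benefit of the care.

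**Simulation.** One active arm against control, unit SD, higher score is better, care more likely after a poor interim score, 600,000 to 2,000,000 children per setting. There are two set-ups:

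- T: care is given if the interim score is below a threshold. Each score depends on the previous one with correlation 0.5.
- U: uptake is fixed by arm, and care is probabilistic given the interim score. Baseline correlates 0.5 with both later scores; interim and outcome correlate 0.625.

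| Set-up | Uptake control v active | True effect | Effect of other care | ITT | Adjusted | Shift |
|---|---|---|---|---|---|---|
| T, same threshold | 16% v 7% | 0.50 | 0 | 0.50 | 0.43 | −0.07 |
| T, same threshold | 16% v 7% | 0.50 | 0.25 | 0.48 | 0.43 | −0.05 |
| T, same threshold | 31% v 16% | 0.50 | 0 | 0.50 | 0.39 | −0.11 |
| U | 30% v 10% | 0.50 | 0 | 0.50 | 0.40 | −0.10 |
| U | 30% v 10% | 0.50 | 0.5 | 0.40 | 0.40 | 0.00 |
| U | 40% v 10% | 0.50 | 0 | 0.50 | 0.35 | −0.15 |
| U | 10% v 30% | 0.50 | 0 | 0.50 | 0.60 | +0.10 |
| T, easier threshold in active arm | 16% v 31% | 0 | 0 | 0.00 | 0.11 | +0.11 |
| T, easier threshold in active arm | 16% v 31% | 0 | 0.25 | 0.04 | 0.11 | +0.07 |
| T, easier threshold in active arm | 16% v 16% | 0.50 | 0.25 | 0.50 | 0.50 | 0.00 |
| U | 10% v 10% | 0.50 | any tried | 0.50 | 0.50 | 0.00 |

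Check of the identity on the fourth row: k = −0.50, so −0.50 × (0.30 − 0.10) = −0.10.

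With set-up T changed to a correlation of 0.5 between all occasions, 16% v 7% gives 0.45 against a true 0.50, and the null case with 16% v 31% gives 0.07 (no effect of other care in both).

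In the fifth row the adjusted and ITT estimates agree at 0.40, but both lie 0.10 below the direct effect of 0.50. The adjustment therefore does not recover the effect in the absence of other care.

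**Consequence for power**, with the standard error held at 0.178: at 0.45, Φ(0.45/0.178 − 1.96) = 0.71; at 0.40, 0.61. Under a null with a spurious 0.11, the chance of significance in that direction is 0.09 instead of 0.025.

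**The case against.** **The method is not named.** The commitment mentions no covariate or model and does not say whether the analysis is primary or secondary. The mixed model under Statistical analyses lists no treatment-received term, the Discussion's wording would fit a sensitivity analysis, and an article condenses a fuller document. This stands as a limit on confidence: if only a supplementary analysis is meant, the primary effect is unharmed. It does not remove the point, because covariate adjustment is the plain meaning, nothing restricts it, and other care is missing from the listed secondary analyses.

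**A reader might infer that the article contradicts its own intention-to-treat statement.** It does not. That statement concerns the population, and a covariate neither removes nor reassigns anyone. The tension is with the effect that such an analysis is meant to give.

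**A reader might also infer that the adjustment necessarily biases the result, or that the plan arranges unequal referral.** Neither is supported. Hospitals are only advised to wait, families may seek treatment, acute care is approved, and outside support is anticipated in every arm. Untreated controls may need more care while the advice lowers what they get, and the two can cancel, as the 16% v 16% row shows. With low uptake (7% v 2%, other care worth 0.25) the adjusted and ITT estimates are only 0.46 and 0.49.

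**The shifts are modest against the trial's precision.** A shift of 0.11 is 0.11/0.178 = 0.62 standard errors. That is fair, but it is a systematic error, and the design has only its nominal 0.80 power at d = 0.5.

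**Conclusion.** The point holds as a should-fix, with moderate confidence. As written, the article allows the treatment comparison to be adjusted for care that follows randomisation and can depend on allocation and need. Such an adjusted group-by-time term need not estimate the effect of assignment, although the analysed population is unchanged.

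Size and direction cannot be fixed from the article. For assumed uptake differences of about 10 to 20 percentage points and no effect of other care, the shift is about 0.05 to 0.11 SD; it reaches 0.15 at a 30-point difference (40% v 10%). It becomes smaller as other care itself becomes more effective, and it is zero at equal uptake. All of this rests on assumed uptake, an assumed care effect and the assumption that poor functioning drives care.

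**What to change.** Replace the commitment to control for other treatment with three statements:

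1. The primary model compares the assigned arms, uses all outcomes regardless of other psychological care, and contains no post-randomisation covariate.
2. Other psychological care is reported by arm.
3. Any analysis that accounts for other care is labelled supplementary, states the question it answers (for example, the effect had no other care been given), and uses a method suited to confounding that arises after randomisation. Multiple imputation of outcomes after such care starts, or inverse-probability weighting, are options and not requirements.

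The Discussion sentence should point to the same statements. The cost is a change of wording and, if wanted, one supplementary analysis. The data are already to be documented, and the sample size does not change. This concerns the analysis only, not whether such care is given.
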